**Confidentiality**

Only local P.I. will have access to the electronic database with an assigned personal account and password. Subjects will be identified by sex, birth date, and assigned trial number, during and after the trial, in accordance with personal data protection law.

**Access to data**

The principal investigator of each site will have complete access to the final trial dataset, and no contractual agreement exists to limit such access for the investigators.

**Dissemination policy**

The results of the trial are expected to be published in a scientific journal and to be presented in medical seminars and conferences. The final reporting will follow the CONSORT Report guidelines (<http://www.consort-statement.org>).

**Discussion**

There are unique features of this trial compared to prior studies on prevention of heat loss at birth in very preterm infants. International guidelines for neonatal resuscitation recommend putting very preterm infants in a plastic wrap immediately at birth without drying (9,10), but the potential advantages of combining those interventions (drying and wrapping) are not considered. In this trial, we will compare two modalities of thermal management (plastic wrapping with or without drying) for preventing heat loss at birth in very preterm infants. The results of this study will allow to cover this gap of knowledge and, possibly, will help to improve thermal management of very preterm infants at birth that remains an unresolved matter in high and low-resource settings.

**Trial status**

The trial is being submitted to the Ethics Committees of the coordinator center and, subsequently, to the Ethics Committees of the participating hospitals.

### **Competing interests**

The authors declare that they have no competing interests.

### **Authors' contributions**

All authors have made substantial contributions to the conception and design of the study protocol and have given final approval of the actual version. FC has prepared the statistical design, including the sample size calculation, and has given the approval of the actual version. All authors read and approved the actual version of the protocol.

## 1 Abbreviations and Definitions

|      |                              |
|------|------------------------------|
| ITT  | Intention-to-treat           |
| NICU | Neonatal Intensive Care Unit |
| SAE  | Serious adverse event        |
| SAP  | Statistical Analysis Plan    |

## 2 Introduction

### 2.1 Summary

The maintenance of thermal homeostasis is a milestone in neonatology (1). Hypothermia at delivery has been clearly associated with adverse neonatal outcomes, but the incidence of hypothermia in very preterm infants at the time of admission to neonatal intensive care unit (NICU) in Europe remains still high (2). Although international guidelines for neonatal resuscitation suggest several interventions to prevent thermal loss at birth in very preterm infants (such as adequate room temperature, use of infant warmers, polyethylene bags/wrap, pre-heated mattresses, caps and heated and humidified gases), a proportion of very preterm infants are hypothermic at NICU admission, hence suggesting the need for further interventions (3,4). Drying is recommended for the thermal management of infants with gestational age >32 weeks (3,4), but this procedure is not indicated for very preterm infants who should be put in a plastic wrap immediately at birth without drying. This indication is based on studies comparing wrapping without drying vs. drying without wrapping (5,6), following previous investigations on plastic wrapping which were not carried out in the delivery room environment (7,8). However, the potential advantages of combining drying and wrapping were not explored. A previous study investigated the role of drying before wrapping in the thermal management of preterm infants, and found comparable temperatures after birth in infants wrapped after being dried and in those wrapped without drying (9). However, no information is currently available for very preterm infants, who are at higher risk of heat loss due to evaporation (10).

### 2.2 Purpose of the analyses

These analyses will compare two approaches of thermal management (plastic wrapping with drying vs. plastic wrapping without drying) for preventing heat loss at birth in very preterm infants. These analyses will be included in the clinical study report.

## 3 Study Objectives and Endpoints

### 3.1 Study Objectives

To compare two approaches of thermal management (plastic wrapping with drying vs. plastic wrapping without drying) for preventing heat loss at birth in very preterm infants.

### 3.2 Endpoints

Primary:

- To compare the proportion of neonates in the normal thermal range (temperature 36.5-37.5°C) at NICU admission.

Secondary:

- To compare the proportion of neonates with hypothermia (temperature  $<36.5^{\circ}\text{C}$ ) at NICU admission;
- To compare the proportion of neonates with moderate-severe hypothermia (temperature  $<36.0^{\circ}\text{C}$ ) at NICU admission;
- To compare the proportion of hyperthermic neonates (temperature  $>37.5^{\circ}\text{C}$ ) at NICU admission;
- To compare the temperature at 1 hour after NICU admission;
- To compare the proportion of intraventricular hemorrhage (all grades and grade III-IV);
- To compare the proportion of respiratory distress syndrome (RDS);
- To compare the proportion of late onset sepsis;
- To compare the proportion of bronchopulmonary dysplasia;
- To compare the mortality before hospital discharge.

## 4 Study Methods

### 4.1 General Study Design and Plan

The study is a multicenter, unblinded, randomized controlled trial. The study will be conducted at 21 Italian Level III hospitals (see list in the trial protocol). The participants will be very preterm infants (inclusion and exclusion criteria are listed in section 4.2). Participants will be randomly assigned to intervention (drying before plastic wrapping) or control (plastic wrapping without drying) arms (randomization is described in section 4.3). Participants will be followed-up until death or discharge.

### 4.2 Inclusion-Exclusion Criteria and General Study Population

Inborn infants fulfilling the following inclusion criteria will be eligible to participate in the study: inborn baby, estimated birth weight  $<1,500\text{ g}$  and/or gestational age  $\leq 30+6$  weeks, parental consent. Infants with major malformations (incompatible with sustained life or affecting the airways) will be excluded.

### 4.3 Randomization and Blinding

Participants will be randomly allocated to intervention or control arms in a 1:1 ratio according to a computer-generated, randomized sequence for each participating hospital. Infants of multiple pregnancies will be randomized as individuals. Randomization (with blocks of size 4-6) will be stratified by center. The randomized allocation will be concealed in double-enclosed, opaque, sealed, and sequentially numbered envelopes. In the delivery room/operating room, the next sequential randomization envelope will be opened only when the neonate will be considered eligible by the attending team, and the assigned procedure will be performed. Contamination between arms will not be allowed. Due to the characteristics of the intervention, neither caregivers nor outcome assessors will be masked to treatment allocation. However, the statistician who will perform data analysis will be blind for treatment allocation.

## 4.4 Study Variables

During the study, data will be collected about: patient anonymized identification and arm assignment; antenatal records (i.e. mother's age, pregnancy complications, ...); birth information (i.e. delivery mode, temperature of delivery/operation room ...); contamination between arms (details and reasons); demographics (i.e. gestational age, birth weight, ..); thermal interventions; respiratory support; outcome measures associated with the endpoints; serious adverse events; discharge information.

## 5 Sample Size

Based on literature data (11), we hypothesize that the proportion of neonates in the normal thermal range at NICU admission may increase from 40% in the control arm to 55% in the intervention arm. With a power of 80% and an error I type of 0.05, the minimum sample size is estimated in 346 neonates (173 per arm). As the design is a stratified multicenter individually randomized trial, randomization is balanced and stratified on centers, and we expect no loss of power as a result of randomizing neonates by center (12). Sample size calculations were performed using R 4.1 software (R Foundation for Statistical Computing, Vienna, Austria) (13).

## 6 General Considerations

### 6.1 Timing of Analyses

The final analysis will be performed at the end of the enrolment or after stopping of the trial as suggested by the monitoring board.

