### **Procedure**

Written and oral information will be offered to parents by the attending physician at maternal admission to the obstetrical ward or before delivery. After obtaining parental consent, all infants with estimated birth weight <1500 g and/or gestational age  $\leq 30^{+6}$  weeks will be assigned to be managed with or without drying before plastic wrapping in the delivery room immediately after birth. Axillary maternal temperature will be measured by a digital thermometer (C202; Terumo,

Tokyo, Japan) about 30 minutes before delivery. Room temperature will be measured at the time of delivery by using a wall thermometer (Oregon Scientific RMR262) in all the study sites.

Patients allocated in both arms will be managed based on the current guidelines for neonatal resuscitation that include the following steps:

- Maintain room temperature at least 24°C;
- Delayed cord clamping (>30 seconds) in uncompromised infants;
- Place the neonate under the radiant infant warmer with the power output set at maximum;
- Cover the body with a plastic bag/wrap up to the shoulders (with or without drying according to the randomized assignment);
- Cover the head of the baby with a cap;
- Use a pre-warmed mattress (optional);
- Use heated and humidified gases (optional).

In case of assignment to the treatment arm, the infant will be dried with a pre-warmed towel before plastic wrapping. In case of assignment to the control arm, the infant will not be dried before plastic wrapping.

All the other interventions, including CPAP, mechanical ventilation, supplemental oxygen concentrations, administration of chest compressions and/or medications will follow the current guidelines for neonatal resuscitation and the decision will be taken by the neonatal team.

At the end of the stabilization, the patient will be transferred to the NICU in a transport incubator (with the temperature set at 37°C).

In all participants, axillary temperature will be measured at 3 time points with a digital thermometer (C202; Terumo, Tokyo, Japan): a) at the end of the stabilization (before leaving the delivery room); b) at NICU admission (primary outcome); and c) 1 hour after NICU admission. Duration of the study will be until the patient's discharge or death.

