### 6.4 Missing Data

Missing data will be considered, and appropriate imputations will be discussed (and performed when appropriate) with a multidisciplinary approach, in order to taken into account statistical, methodological and clinical aspects of this issue.

Missing data due to the premature discontinuation from the study or treatment are unlikely.

Appropriate measures will be undertaken in order to avoid missing data, including regular double check of completeness of data forms and review of the video recordings.

Missing data will be described in the study report.

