## 8 Analysis of primary outcome measure

The primary outcome measure is the proportion of neonates in the normal thermal range (temperature 36.5-37.5°C) at NICU admission. It will be summarized as frequency with percentage for each arm. In the unadjusted analysis, it will be compared between the two arms using Chi Square test or Fisher's test. The adjusted analysis will involve a generalized mixed-effect regression model including the trial arms (fixed effect), the participating center (random effect) and unbalanced participant characteristics at baseline (fixed effects). Relative risk with 95% confidence intervals for treatment vs. control arms will be calculated in both unadjusted and adjusted analyses, with a confidence interval higher than 1 indicating superiority of the intervention over the control.

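### SAP 6.1 sets the final analysis at the end of enrolment, but follow-up runs to discharge or death, so read literally the outcomes that run through the hospital stay would be incomplete for infants still in hospital.

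*Combined protocol and SAP*

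**What the plan says.** On the timing of the final analysis there is a single statement, in SAP 6.1: "The final analysis will be performed at the end of the enrolment or after stopping of the trial as suggested by the monitoring board". The protocol's Statistical analysis section gives no timing.

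On follow-up, SAP 4.1 says "Participants will be followed-up until death or discharge", and the protocol's Procedure section says "Duration of the study will be until the patient's discharge or death".

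The secondary endpoints in SAP 3.2 include three that depend on the hospital course: "To compare the mortality before hospital discharge", "To compare the proportion of bronchopulmonary dysplasia" and "To compare the proportion of late onset sepsis". No assessment time is stated for the last two. Unexpected death is also one of the three types of serious adverse event compared between arms in the SAP's Safety Analyses section.

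Neither document mentions a database lock, a wait for the last discharge, or a staged analysis with the primary outcome first. SAP 6.4 leaves imputation to later discussion and has no rule for an infant who is still in hospital when the data are cut.

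**The concern.** Infants are randomised at birth, so enrolment ends when the last infant is born and assigned. At that moment this infant has almost no follow-up, and others born in the preceding weeks are still in hospital. Whether they survive to discharge is unknown, and sepsis or bronchopulmonary dysplasia may still be diagnosed.

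A statistician who followed SAP 6.1 to the letter would have to decide how to handle these infants without a pre-specified rule, possibly after seeing data. Counting them as event-free lowers the reported rates. Excluding or imputing them loses information on outcomes that the trial set out to collect in full. Infants with long stays are over-represented among those in hospital on any given day, so the affected infants are not a random sample.

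The wording also covers an early stop. The interim analysis uses the first 100 infants, and after a stop at that point a larger share of the infants could still be in hospital.

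**Working it through.** **1. The plan's own figure.** Inputs from SAP 5 and 6.2: 40% versus 55%, 80% power, two-sided 0.05, 1:1 allocation. With pooled variance and no continuity correction:

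n per arm = [1.960 × √(2 × 0.475 × 0.525) + 0.842 × √(0.40 × 0.60 + 0.55 × 0.45)]² / 0.15² = 172.8, rounded up to 173, or 346 in total.

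The stated size reproduces, and power at 173 per arm is 80.0%. The timing point does not alter it, because the primary outcome is fixed at NICU admission: "The primary outcome measure is the proportion of neonates in the normal thermal range (temperature 36.5-37.5°C) at NICU admission".

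**2. Which outcomes are exposed at the end of enrolment.**

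- Complete within about an hour of the last admission: the primary outcome, the three secondary outcomes based on admission temperature, and the 1-hour temperature.
- Not determinable for any infant still in hospital: mortality before discharge.
- Possibly incomplete for infants still in hospital: bronchopulmonary dysplasia, late onset sepsis and, for the very last infants, intraventricular hemorrhage.
- Serious adverse events: the two temperature types are essentially complete as far as the scheduled measurements capture them, since these end 1 hour after admission. Unexpected death is the type clearly exposed.

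**3. How many infants.** The documents give neither length of stay nor enrolment period, so both are assumptions. With uniform accrual:

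expected number in hospital at the end of enrolment = 346 × mean stay (weeks) / enrolment (months × 52/12 weeks)

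| Enrolment | 4-week stay | 8-week stay | 12-week stay |
|---|---|---|---|
| 9 months (39 weeks) | 35 (10%) | 71 (21%) | 106 (31%) |
| 12 months (52 weeks) | 27 (8%) | 53 (15%) | 80 (23%) |
| 18 months (78 weeks) | 18 (5%) | 35 (10%) | 53 (15%) |
| 24 months (104 weeks) | 13 (4%) | 27 (8%) | 40 (12%) |
| 36 months (156 weeks) | 9 (3%) | 18 (5%) | 27 (8%) |

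Examples: 346 × 8/52 = 53; 346 × 8/104 = 27; 346 × 12/39 = 106; 346 × 4/156 = 9.

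For mortality before discharge the table gives the expected number undetermined. For the other outcomes it is an upper bound, because some events will already be on record.

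**4. Early stop.** Under the same assumptions with an 8-week stay, the number in hospital when the 100th infant is enrolled is 346/52 × 8 = 53 of 100 (12-month accrual) or 346/104 × 8 = 27 of 100 (24-month accrual). Infants enrolled while the interim analysis is under way would reduce these shares. SAP 6.1 says only that analysis comes after the stop and sets no interval, so this is an illustration of what an immediate cut would mean.

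**The case against.** The best defence is that SAP 6.1 is loosely worded and merely separates the final analysis from the interim one. Several places point towards complete follow-up: both statements that infants are followed to discharge or death, the discharge information listed in SAP 4.4, and the protocol's requirement to follow serious adverse events until they resolve or are judged chronic or the infant stable. SAP section 13 adds that the SAP changes nothing in the protocol's statistical approach.

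This reading is plausible, and the team may well intend it. Nothing in the documents confirms it, however. SAP 6.1 is the only timing rule, and section 13 cannot repair it because the protocol has no timing rule to fall back on.

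Other parts of the defence do stand, against four stronger conclusions that a reader might infer:

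- *That event rates will be understated.* This follows only if undischarged infants are counted as event-free. No text instructs that; treating them as missing need not lower the rates.
- *That the whole safety comparison is truncated.* Only unexpected death is clearly exposed among the three types of serious adverse event.
- *That the trigger contradicts the SAP's own missing-data statement.* SAP 6.4 says "Missing data due to the premature discontinuation from the study or treatment are unlikely". An infant still in hospital has not discontinued, so the statement does not address this case in either direction.
- *That the treatment comparison is biased.* Randomisation is 1:1 in blocks of 4 to 6 within center, so the cut should fall similarly on both arms.

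**Conclusion.** The conflict between SAP 6.1 and the follow-up statements is real and should be corrected before the analysis. Followed as written, the rule leaves mortality before discharge, bronchopulmonary dysplasia, late onset sepsis and unexpected death incomplete for the infants still in hospital, with no stated way to count them.

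Its size cannot be fixed from the documents. The range of 3% to 31% of 346 infants rests on assumed uniform accrual, stays of 4 to 12 weeks and enrolment over 9 to 36 months; no single cell of the table should be read as a forecast.

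The consequence is limited to lost information, or understated absolute rates under one way of counting, for secondary and late safety outcomes. The documents do not support reading this as a threat to the primary result: admission temperature, the 80% power and the other temperature outcomes are essentially untouched.

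**What to change.** Replace the sentence in SAP 6.1 with, for example: *Final analysis takes place once the last randomised infant has died or been discharged and the database has been locked; after an early stop it likewise waits for every infant randomised by then.*

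This brings SAP 6.1 into line with SAP 4.1 and the protocol's Procedure section. It changes no sample size, test or trial procedure. The cost is that the final report waits for the last infant's discharge, which the protocol's follow-up already requires.

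If the team wants the primary result sooner, the alternative is a pre-specified staged analysis: temperature outcomes first, in-hospital outcomes after the last discharge, with a written rule for any infant not yet discharged at a data cut. That takes more drafting than the one-sentence change.

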### 6.2 Approach for main analysis

Data analysis will be performed using the statistical software packages R. All tests will be two-sided and a p-value less than 0.05 will be considered statistically significant. Statistical analysis will include an unadjusted analysis followed by an adjusted analysis.

Analysis will be performed according to the "intention to treat" (ITT) approach. In case of deviations from the protocol regarding the contamination between arms, a per-protocol analysis will be also performed, and the conclusion will be drawn according to the results of both analyses.

Additional sub-group analyses will be considered with exploratory purpose.

### 6.3 Additional analysis

A sub-analysis according to gestational age (23+0-27+6 and 28+0-31+6 weeks) will be performed with exploratory purpose.

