## Background

The maintenance of thermal homeostasis is a milestone in neonatology (1-4). A significant association between hypothermia at delivery and adverse neonatal outcomes has been clearly demonstrated (5-8), but the incidence of hypothermia in very preterm infants at the time of admission to neonatal intensive care unit (NICU) in Europe remains still high (8).

International guidelines for neonatal resuscitation suggest several interventions to prevent thermal loss at birth in very preterm infants, such as adequate room temperature, use of infant warmers, polyethylene bags/wrap, pre-heated mattresses, caps and heated and humidified gases (9,10). Nevertheless, a certain percentage of very preterm infants are hypothermic at the time of the NICU admission suggesting that, in addition to the actual standard of care, further interventions are needed (4,9,10).

While drying is recommended for the thermal management of infants with gestational age  $>32$  weeks (9,10), this procedure is not indicated for very preterm infants who should be put in a plastic wrap immediately at birth without drying. Of note, such indication is based on studies comparing wrapping without drying vs. drying without wrapping (11,12), following previous investigations on plastic wrapping which were not conducted in the delivery room environment (13,14). However, the potential advantages of combining those interventions (drying and wrapping) were not explored. To our knowledge, only one study investigated the role of drying before wrapping in the thermal management of preterm infants, and found comparable temperatures after birth in infants wrapped after being dried and in those wrapped without drying (15). No data are currently available for very preterm infants, who are at higher risk of heat loss due to evaporation (16). We hypothesized that drying before wrapping could prevent heat loss immediately after birth and reduce hypothermia at NICU admission in very preterm infants.

The “PICOT” question of this study is:

P: in very preterm infants,

I: does drying before plastic wrapping in the delivery room,

C: compared to standard of care (plastic wrapping without drying),

O: increase the percentage of infants in the normal thermal range (temperature 36.5-37.5°C),

T: at the time of admission to the NICU?

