### **Inclusion criteria**

Infants satisfying the following inclusion criteria will be eligible to participate in the study:

1. Estimated birth weight <1500 g and/or gestational age  $\leq 30^{+6}$  weeks (and)
2. Inborn (and)
3. Parental consent; a written informed consent will be obtained by a member of the neonatal team involved in the study from a parent or guardian at the maternal admission to the Obstetric Department.

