## 10. Exploratory Analyses

The outcome measures will be compared between the trial arms within strata of interest: participants with gestational age between 23+0 and 27+6 weeks, and participants with gestational age between 28 and 31+6 weeks). These analyses will be performed with exploratory purpose.

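### The exploratory gestational-age strata leave out some eligible infants, and arm comparisons within each stratum cannot show whether the effect of drying differs by gestational age

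*Combined protocol and SAP*

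**What the plan says.** **Eligibility.** The protocol's inclusion criteria begin "Estimated birth weight <1500 g and/or gestational age" and set the gestational limit at 30+6 weeks or less. Either condition is enough. The protocol's Procedure section and SAP section 4.2 repeat the rule. No exclusion concerns gestational age: the protocol excludes major congenital malformation, outborn birth and parental refusal, and the SAP says "Infants with major malformations (incompatible with sustained life or affecting the airways) will be excluded".

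**Strata.** SAP section 6.3 gives the two bands: "A sub-analysis according to gestational age (23+0-27+6 and 28+0-31+6 weeks) will be performed with exploratory purpose". The protocol's Statistical analysis section and SAP section 10 (Exploratory Analyses) use the same bands.

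**Method.** SAP section 10 supplies it: "The outcome measures will be compared between the trial arms within strata of interest". It adds: "These analyses will be performed with exploratory purpose". The regression models in SAP sections 8 and 9 contain arm, centre and unbalanced baseline characteristics. No arm-by-gestational-age term appears in either document.

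**Significance rule.** SAP section 6.2 states: "All tests will be two-sided and a p-value less than 0.05 will be considered statistically significant". Exploratory comparisons are not exempted.

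**The concern.** There are two separate weaknesses.

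First, the bands do not match the population that the trial admits. An infant of 32+0 weeks or more with an estimated weight below 1500 g is eligible, and so is an infant below 23+0 weeks, but neither has a stratum. The upper bound of 31+6 is also not an eligibility limit: the gestational criterion stops at 30+6, and infants of 31+0 to 31+6 enter only by weight. The plan does not say whether leaving the others out is intended.

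Second, two p-values, one per stratum, do not measure a difference between strata. Each stratum is smaller than the trial and has well under 80% power for the planned effect, so one significant and one non-significant result is a likely outcome even when drying works equally well in both. Gestational age is the only subgroup factor that the plan names, and the Background motivates the trial by the greater evaporative heat loss of very preterm infants. Readers will look here for a gestational-age effect, and the planned output gives them no valid way to judge one.

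**Working it through.** **1. Coverage, from the criteria**

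| Gestational age (weeks) | Route into the trial | Stratum |
|---|---|---|
| below 23+0 | gestation (no lower limit) | none |
| 23+0 to 27+6 | gestation | lower |
| 28+0 to 30+6 | gestation | upper |
| 31+0 to 31+6 | weight only | upper |
| 32+0 and above | weight only | none |

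The documents do not give the number in the two uncovered rows. As an assumption, a share of 0–20% of 346 is 0–69 infants (5% = 17, 10% = 35, 20% = 69).

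**2. The plan's own sample size**

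Inputs from SAP section 5: normothermia "may increase from 40% in the control arm to 55% in the intervention arm", 80% power, type I error 0.05, 173 per arm. SAP section 6.2 makes tests two-sided.

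With the average proportion (0.40 + 0.55)/2 = 0.475:
- null term: √(2 × 0.475 × 0.525) = 0.706
- alternative term: √(0.40 × 0.60 + 0.55 × 0.45) = 0.698
- n per arm = [(1.96 × 0.706 + 0.842 × 0.698)/0.15]² = 172.8, rounded up to 173

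The stated 346 is reproduced, with power 80.0%.

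**3. Power inside a stratum, same true effect in both**

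Power(n per arm) = Φ[(0.15√n − 1.96 × 0.706)/0.698]. The chance that exactly one of two independent strata is significant is a(1 − b) + b(1 − a), where a and b are the two powers. The splits are assumptions. With all 346 infants inside the strata:

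| Split lower:upper | n per arm | Power a, b | Exactly one significant |
|---|---|---|---|
| 30:70 | 51.9, 121.1 | 33%, 65% | 55% |
| 40:60 | 69.2, 103.8 | 42%, 58% | 51% |
| 50:50 | 86.5, 86.5 | 51%, 51% | 50% |

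For 30:70: 0.332 × 0.351 + 0.649 × 0.668 = 0.55.

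If 20% of infants fall outside the strata, power becomes 28% and 55% (30:70) to 42% and 42% (50:50), and exactly one stratum is significant in 49–52% of trials. Over all the scenarios the range is 49–55%.

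**4. What an interaction test could do**

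Take all 346 infants in two covering strata, 40% versus 55% in one and 40% versus 40% in the other. On the risk-difference scale the standard error of the difference between the two effects is √[(0.24 + 0.2475)/n₁ + (0.24 + 0.24)/n₂], and power is Φ(0.15/SE − 1.96).
- 50:50: SE = 0.1058, power = Φ(−0.54) = 29%
- 40:60: SE = 0.1080, power 28%
- 30:70: SE = 0.1156, power = Φ(−0.66) = 25%

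For 80% power the same formula needs about 1,350 infants (50:50) to 1,610 (30:70).

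The plan reports risk ratios, so the log scale was checked too. The contrast is ln(0.55/0.40) = 0.318. At 50:50 the variance is 0.45/(0.55 × 86.5) + 3 × 0.60/(0.40 × 86.5) = 0.0615, so SE = 0.248 and power = Φ(0.318/0.248 − 1.96) = 25%. The message is the same.

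**The case against.** **The analysis is exploratory.** Both documents say so, and SAP section 6.2 says the same of subgroup analyses generally. This stands and limits the consequence. Infants outside the bands are missing from a side analysis only; they remain in the intention-to-treat comparison. A reader might infer that randomised infants are lost to the trial's conclusions. The documents do not support that.

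**The plan never promises a between-stratum conclusion.** This is also correct. No section says that a gestational-age difference will be declared if one stratum is significant and the other is not. The 49–55% figure describes how often the planned output would look like effect modification when there is none. It is not the error rate of a stated decision rule.

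**The bound of 31+6 may be deliberate.** It lies just below the 32-week point in the Background, which says "While drying is recommended for the thermal management of infants with gestational age" above 32 weeks. Restricting the strata to infants below that point would suit a question about very preterm infants. The documents do not give this reason, however, so the restriction is unexplained, and it would not account for infants below 23+0.

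**A tempting stronger reading.** One might claim that the protocol contradicts itself, because both arms are to follow current guidelines while control infants above 32 weeks are not dried. The Procedure section does not support this: its list of guideline steps makes drying depend on the randomised assignment. What remains is that a weight-only entry route sits loosely with the label "very preterm". That is a question of population wording, separate from this point.

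**The interaction will rarely be decisive.** With 25–29% power, a non-significant interaction is weak evidence of a uniform effect. That is a reason to report an interval and to avoid two separate verdicts; it does not rescue the within-stratum tests.

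**Conclusion.** The point holds as a limited flaw in an exploratory analysis, worth correcting because correction is almost free.

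The coverage gap follows from the criteria alone and needs no assumption. Its size cannot be derived from the documents: the 0–69 infants shown are illustrative, and the true number could be near zero.

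The planned comparisons cannot show whether the effect varies with gestational age. The figure of about one half rests on the planned 40% versus 55% applying equally in both strata, splits from 30:70 to 50:50, up to 20% of infants outside the strata, and a normal approximation for the primary outcome without adjustment for centre. It barely moves across that range.

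The primary intention-to-treat analysis and the sample size of 346 are unaffected.

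**What to change.** 1. In the protocol's Statistical analysis section and SAP sections 6.3 and 10, define strata that place every randomised infant, for example below 28+0 and 28+0 or more weeks. Report the number at 32+0 weeks or more, so that readers can see how far the upper stratum extends. If leaving these infants out is intended, state the restriction and its reason, and report how many are left out.
2. In SAP section 10, add an arm-by-gestational-age interaction to the model. Report the ratio of risk ratios with its 95% confidence interval, and base any statement about subgroup difference on it. Show stratum risk ratios with intervals descriptively, without separate significance verdicts.
3. State that the trial is not powered for the interaction, so that a non-significant result is not read as proof of a uniform effect.

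The cost is a few lines of wording and one model term. Gestational age is already collected (SAP section 4.4), so no new data are needed. The downside is an imprecise interaction estimate, which has to be presented as such.
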